### Objectives

The specific objectives are:

To confirm that GTN patch application for 30 - 60 minutes increases the radial artery diameter of neonates.To confirm that it is safe to apply a GTN patch for 30 - 60 minutes for neonates.To estimate the mean values of the within-patient changes in the peripheral artery diameter from baseline to inform the choice of the optimal duration of GTN patch application in the context of cannulation in neonates.To evaluate the feasibility of a proposed future trial design to assess the impact of GTN patches on first-attempt cannulation rates in terms of recruitment and data collection.

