#### Trial hypothesis being tested:

The topical application of GTN for 30 - 60 minutes increases the radial artery diameter compared to no application.

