### Interventions

Glyceryl trinitrate 5mg (Transiderm-Nitro patch, 5mg/24 hours) will be applied for 30 minutes, 45 minutes or 60 minutes. Neonates will be allocated to either the GTN Group or the Control Group. Glyceryl trinitrate is a registered medication in the Australian Therapeutic Goods Registry. The Therapeutic Goods Administration (TGA) has been notified about this clinical trial (Reference number: CT-2023-CTN-02133-1).

GTN Group: for neonates in this group, a GTN patch (5mg) will be applied at the site of radial artery cannulation for 30 minutes (Group A, n = 15), 45 minutes (Group B, n = 15) or 60 minutes (Group C, n = 15). Immediately after its application, the GTN patch will be covered with a Coban™ adhesive bandage to ensure blinding.

Control Group: for neonates in this group (Group D, n = 15), a Coban™ adhesive bandage with no intervention will be applied to the bare skin at the site of the radial artery for 30 minutes (n = 5), 45 minutes (n = 5) or 60 minutes (n = 5) to ensure blinding.

Only one arterial site per infant will be studied to ensure that the samples are independent.

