### Outcomes

#### Primary outcome:

the primary outcome will be the change in the postintervention radial artery diameter from baseline. This will be compared between the GTN and Placebo Groups.

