### Sample size

We aim to recruit 60 patients (15 in each arm: 1 control and 3 GTN arms) over 12 months, which is achievable given that we expect approximately 250 eligible patients to be admitted to the neonatal ICU each year.

Justification of the sample size is based on the desire to demonstrate that reasonable vasodilation with GTN patch application is achievable in our target study population. We assume that the measures of the radial artery diameter in study participants will have a mean of 0.76mm without treatment and a common within-group standard deviation of approximately 0.18mm, as observed in a reference study of neonates aged 0 - 6 months.^(12)^ With a sample size of 15 for each group (1 control and 3 GTN patch groups), the margin of error around the corresponding estimated population mean diameters is less than 1 mm, and an omnibus one-way ANOVA would have more than 80% power to determine whether GTN patch application increases the radial artery diameter when the minimum mean of the treatment group differs from that of the control group by approximately 0.19mm (alpha = 0.05). Analyses based on the change from baseline, which is our primary outcome, are expected to be more powerful than analyses assessing the cross-sectional diameters, and the detectable cross-sectional difference of 0.19mm corresponds to an approximate 25% increase from the estimated baseline value, which is of the order previously observed in children aged 0 - 2 years receiving subcutaneous injections of GTN,^(11)^ and substantially less than that observed after patch application in children aged 2 - 8 years (average increase of 40% in the radial artery diameter after 30 minutes and an increase of 70% after 1 hour).^(10)^ Furthermore, power will be increased by extending the assessment of GTN-induced vasodilation to an ANCOVA that reduces residual variation by adjusting for key demographic/clinical correlates of arterial diameter.

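### The plan describes both a two-group and a four-group comparison, and the primary ANCOVA does not settle which applies or include the randomised patch duration

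*Protocol article*

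**What the plan says.** All references are to the protocol article.

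- **Objectives.** The third objective is to estimate mean within-patient changes in diameter "to inform the choice of the optimal duration of GTN patch application in the context of cannulation in neonates". It is an estimation objective and sets no test or selection rule.
- **Trial hypothesis.** The durations are taken together: "The topical application of GTN for 30 - 60 minutes increases the radial artery diameter compared to no application".
- **Interventions.** The patch is applied "for 30 minutes (Group A, n = 15), 45 minutes (Group B, n = 15) or 60 minutes (Group C, n = 15"). The single control group, Group D, has a bandage only, "for 30 minutes (n = 5), 45 minutes (n = 5) or 60 minutes (n = 5) to ensure blinding".
- **Primary outcome.** Of the change from baseline: "This will be compared between the GTN and Placebo Groups".
- **Table 2.** One GTN column (n = 45) and one control column (n = 15).
- **Sample size.** Four groups: "With a sample size of 15 for each group (1 control and 3 GTN patch groups"). Power is for an omnibus one-way ANOVA, and the text then speaks of extending the assessment to an ANCOVA with demographic and clinical covariates.
- **Table 3.** The primary outcome is assigned ANCOVA. The number of group levels is not given, and no outcome has a duration term or duration contrast.

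**The concern.** Duration is a randomised factor and the subject of an objective, so the primary model should show how it is handled. Two descriptions compete. On the two-group reading, any true difference between 30, 45 and 60 minutes stays in the residual and widens the interval for the main GTN effect. On the four-group reading, the test is an omnibus F test, which is not the GTN-versus-control comparison that the hypothesis and primary outcome describe, and which has different power.

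On either reading, the duration objective has no modelled contrast behind it. It rests on raw changes within Groups A, B and C. Each raw change combines the GTN effect with whatever else happens over that time under a bandage, and no stated analysis sets a GTN duration beside the controls that shared it. The duration chosen for the later trial would draw on these estimates.

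**Working it through.** **Inputs from the protocol.** Control mean 0.76 mm, SD 0.18 mm (cross-sectional diameter), difference 0.19 mm, alpha 0.05, four groups of 15 (Sample size); durations 15/15/15 in GTN and 5/5/5 in control (Interventions); a rise of 40% at 30 minutes and 70% at 1 hour in older children (Sample size). No dropout is stated and none is used. The SD of the change from baseline is not given.

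**1. The plan's own figure.** Take means of 0.76 and three times 0.95. The grand mean is 0.9025, so the deviations are -0.1425 and three times 0.0475.
- Noncentrality = 15 × (0.1425² + 3 × 0.0475²) / 0.18² = 12.53.
- Noncentral F on 3 and 56 df: power **83.0%**. The stated figure of more than 80% reproduces, as a four-group test.

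**2. The same trial read as two groups.**
- SE = 0.18 × √(1/45 + 1/15) = 0.18 × 0.298 = 0.0537 mm.
- Noncentrality = 0.19 / 0.0537 = 3.54 on 58 df: power **93.6%**. The difference detectable with 80% power is 0.153 mm.

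**3. Is the pooled contrast confounded?** Mean time is (30 + 45 + 60)/3 = 45 minutes in GTN and (5×30 + 5×45 + 5×60)/15 = 45 minutes in control. The two distributions are proportional, so treatment and duration are orthogonal. The pooled contrast is **not** confounded with time under the bandage.

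**4. What omitting duration costs.** Assume the cited rises apply, with 55% interpolated at 45 minutes and no change in controls. GTN changes are then 0.304, 0.418 and 0.532 mm, a spread of ±0.114 mm about their mean.
- *No duration term:* the extra residual sum of squares is 30 × 0.114² = 0.390. Residual SD = √[(58 × 0.0324 + 0.390)/58] = 0.198. Half-width = 2.002 × 0.198 × 0.298 = **0.118 mm**.
- *Additive duration factor:* the common fitted step is 0.75 × 0.114 = 0.0855, leaving ±0.0285 in GTN and ±0.0855 in control. The extra sum of squares is 30 × 0.0285² + 10 × 0.0855² = 0.097. Residual SD = √[(56 × 0.0324 + 0.097)/56] = 0.185. Half-width = 2.003 × 0.185 × 0.298 = **0.110 mm**.
- *With interaction:* half-width = 2.005 × 0.18 × 0.298 = **0.108 mm**.
- *If duration has no effect at all:* the half-widths are 0.1074, 0.1075 and 0.1076 mm, so the added terms cost almost nothing.
- *If the SD of change were 0.10 mm (assumed for illustration):* the same formulas give 0.077, 0.065 and 0.060 mm, a larger gain.

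**5. Precision for the duration objective (SD 0.18 mm).**

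| Quantity | SE (mm) | 95% half-width (mm) |
|---|---|---|
| C minus A, raw | 0.18 × √(2/15) = 0.066 | 0.132 |
| C minus A, net of matched controls | 0.18 × √(2/15 + 2/5) = 0.131 | 0.264 |
| GTN minus control at one duration, 15 vs 5 | 0.18 × √(1/15 + 1/5) = 0.093 | 0.186 |
| GTN minus control at 30 or 60 min, interaction linear in minutes | 0.18 × √(1/45 + 1/15 + 1/30 + 1/10) = 0.085 | 0.170 |

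The linear term helps the duration-specific effects a little. It does not help the control-subtracted C minus A difference, whose SE is twice the raw one. One duration against its 5 matched controls has about 49% to 52% power at 0.19 mm.

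**The case against.** **The article is condensed.** Group coding and model terms are commonly left to the SAP, so a missing interaction term alone would be no finding. That stands. What remains is that the article itself describes the comparison in two ways, and its analysis table does not choose between them.

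**The ANCOVA may already have four levels**, as an extension of the four-group ANOVA. This is a fair reading. If it is right, the between-duration variation among the GTN arms is already out of the residual and the precision gain in step 4 does not arise. But the hypothesis and the primary outcome would still need a named GTN-versus-control contrast in place of the omnibus test.

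**A reader might infer that the duration-matched controls are wasted.** The documents do not support this. All 15 controls enter either comparison, the stated purpose of the 5/5/5 split is blinding, and the split is what balances bandage time in the pooled contrast.

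**A reader might infer that the duration comparison is invalid.** It is not. A, B and C are randomised arms, so C versus A fairly compares a covered patch for 60 minutes with one for 30, which is arguably what a clinician choosing a waiting time needs. Separating GTN from elapsed time is a further question. The documents give no figure for drift under a bandage, so no size of bias can be claimed. Replacing the raw changes with control-subtracted ones would double the SE of C minus A. That is a trade-off, and for this reason the control-subtracted estimates should be added and not substituted.

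The contralateral limb is also measured at the same times. It is only a partial time control, since it carries no bandage and may be exposed systemically.

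**Conclusion.** The point holds as an inconsistency with an inexpensive improvement attached, and not as a bias in the primary result. The hypothesis, primary outcome and Table 2 describe two groups, the sample size describes four, and Table 3 does not decide. The difference in power is 83.0% against 93.6% at 0.19 mm.

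Against a two-level model, including duration would narrow the 95% half-width for the GTN effect from about 0.118 to 0.110 mm (additive) or 0.108 mm (with interaction). This rests on an SD of 0.18 mm and on the cited 40% to 70% rise carrying over to neonates. The gain is larger if the SD of change is smaller, and there is virtually no loss if duration does not matter.

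Duration-specific effects net of control will be imprecise with 5 controls per duration and can only be exploratory.

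**What to change.** 1. **Primary outcome and Table 3:** state that the primary ANCOVA includes treatment (GTN or control) and assigned duration (30, 45 or 60 minutes), and that the primary contrast is the GTN-versus-control effect averaged over durations.
2. **Sample size:** align the text with that contrast. On the protocol's inputs its power is about 94% at 0.19 mm if the effect is the same at all durations. The omnibus figure should not stand as the power of the primary comparison.
3. **Third objective:** keep the within-arm changes for A, B and C. Add, labelled exploratory, duration-specific GTN-minus-control changes with 95% confidence intervals from a treatment-by-duration term linear in minutes. Note that only 5 controls share each duration and that control-subtracted differences between durations have about twice the SE of the raw ones.

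The cost is wording and 2 to 3 degrees of freedom. No extra infants or measurements are needed.

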#### Trial hypothesis being tested:

The topical application of GTN for 30 - 60 minutes increases the radial artery diameter compared to no application.

### Study design, setting and time period

This prospective, parallel, single-center randomized controlled trial will be conducted in the neonatal ICU of Perth Children's Hospital (PCH), Child and Adolescent Health Service (CAHS), Perth, Australia. The PCH neonatal ICU is a 30-bed tertiary referral center that provides intensive and high dependency care for critically ill neonates. Over 800 infants are admitted to the PCH neonatal ICU each year, and all infants are born at other hospitals. This study has been approved by the CAHS Human Research Ethics (HREC) and Governance Committees and is on the Australian New Zealand Clinical Trials Registry. The study will aim to recruit eligible patients (n = 60) from July 2023 to July 2024. Newborns’ parents or guardians will be approached, and written informed consent will be obtained. The assessment plan is shown in table 1. This clinical protocol has been prepared according to the SPIRIT 2013 Checklist.^(12)^

**Table 1 t1:** Assessment plan

Informed consent
Inclusion/exclusion criteria review
Randomization
Measurement of the radial artery diameter by ultrasound preintervention by a blinded operator
Application of the GTN patch/bandage with no patch by unblinded nursing staff (not involved in the day-to-day management of the baby) for 30 minutes or 45 minutes or 60 minutes
Blood pressure measurement performed by the bedside nurse every 15 minutes until the end of the intervention
Tracking of oxygen saturation and FiO_2_ requirements by the bedside nurse
Blood gas measurement by the bedside nurse postintervention to measure methemoglobin levels
Removal of the GTN patch/bandage with no patch by unblinded nursing staff (not involved in the day-to-day management of the baby) for 30 minutes or 45 minutes or 60 minutes
Measurement of the radial artery diameter by ultrasound postintervention by a blinded operator

GTN - glyceryl trinitrate; FiO_2_ - fraction of inspired oxygen.

### Inclusion criteria

Neonates born at > 34 weeks of gestation who are admitted to the neonatal ICU at PCH and for whom a peripheral arterial line is needed for sampling or invasive blood pressure monitoring.Neonates born at > 34 weeks of gestation admitted to the neonatal ICU, scheduled to undergo elective or general surgery and for whom peripheral artery cannulation is needed for hemodynamic monitoring or frequent blood sampling (perioperative).

### Exclusion criteria

Neonates who undergo previous radial artery cannulation attempts and those who have hematomas at the cannulation site, abnormal Allen's test results, a hypercoagulable state, coagulopathy, and peripheral vascular disease.Neonates with unstable vital signs, including hypotension, shock or significant arrythmias.Neonates scheduled to undergo cardiac surgery.Neonates with increased intracranial pressure, intracranial hemorrhage, and recent use of sildenafil.Neonates with a visible deformity in the radial artery area.

### Interventions

Glyceryl trinitrate 5mg (Transiderm-Nitro patch, 5mg/24 hours) will be applied for 30 minutes, 45 minutes or 60 minutes. Neonates will be allocated to either the GTN Group or the Control Group. Glyceryl trinitrate is a registered medication in the Australian Therapeutic Goods Registry. The Therapeutic Goods Administration (TGA) has been notified about this clinical trial (Reference number: CT-2023-CTN-02133-1).

GTN Group: for neonates in this group, a GTN patch (5mg) will be applied at the site of radial artery cannulation for 30 minutes (Group A, n = 15), 45 minutes (Group B, n = 15) or 60 minutes (Group C, n = 15). Immediately after its application, the GTN patch will be covered with a Coban™ adhesive bandage to ensure blinding.

Control Group: for neonates in this group (Group D, n = 15), a Coban™ adhesive bandage with no intervention will be applied to the bare skin at the site of the radial artery for 30 minutes (n = 5), 45 minutes (n = 5) or 60 minutes (n = 5) to ensure blinding.

Only one arterial site per infant will be studied to ensure that the samples are independent.

### Justification of the dose of the intervention

Patients randomized to the active arms (Groups A, B and C) will have a GTN patch 5mg (Transiderm-Nitro patch, 5mg/24 hours) applied for 30 minutes, 45 minutes or 60 minutes, and a Coban™ adhesive bandage will be placed over the patch. Minitran 5 has a surface area of 6.7cm^2^ and the amount of glyceryl trinitrate (GTN) released over 24 hours is 5mg. The Transiderm-Nitro transdermal delivery system is designed to provide continuous controlled release of GTN through intact skin to overcome the problems of the short half-life and extensive first-pass metabolism of GTN. The rate of release of GTN is linearly dependent upon the area of the applied system.

The release rate from the patch is 0.2mg/hour. The onset of action of the GTN patch occurs within 30 minutes. It has been shown that GTN levels rise to a steady state within 1 - 2 hours of application of the GTN patch, and the levels wane with a half-life of approximately 30 min after removal of the patch.^(13)^

The studies performed by Hasanin et al. (GTN transdermal patch)^(10)^ and Jang et al. (subcutaneous injection of GTN) were used for pharmacokinetic data and dose selection.^(11)^ Both of these studies used a dose of 2.5 - 5mg/kg/hour. Most of the available data for GTN dosage were derived from adult, not pediatric, studies.^(7,14,15)^ There were no major systemic side effects, such as hypotension and methemoglobinemia, reported in the pediatric studies.^(9)^

### Study endpoint

The primary endpoint of the study is radial artery diameter. After obtaining informed consent from a patient's parent, images of the radial artery will be obtained from the infant's wrist using a portable ultrasound machine. The diameter of the radial artery will be measured using a linear, high-frequency hockey stick probe (6 - 113MHz) with the Philips EPIQ CVx Diagnostic Ultrasound system.

Measurements will be obtained in the short-axis plane of the distal forearm, medial to the border of the styloid process of the radius and at the point with maximal pulsation of the radial artery, with the wrist at a 45º angle.^(16)^ The point will be marked to guide the intervention and ensure coverage of the site over the peripheral artery, which will be measured postintervention. The operator will be an experienced neonatologist blinded to the study group. Measurements will be obtained in both radial arteries at baseline before application of the GTN patch/bandage with no patch and at 30 minutes, 45 minutes or 60 minutes after application.

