#### Blinded staff:

the ultrasound measurements of the radial artery will be performed by an operator who will be blinded to the intervention. In addition, the bedside nurse who measures the blood pressure every 15 minutes until the end of the intervention will also be blinded.

There will be a blinded and unblinded delegation log for blinded and unblinded trial members with their duties listed.

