### Data management

The trial involves the collection of clinical data and radial artery images by ultrasound measurement. They will be stored in a password-protected database on the hospital computer. CAHS health department information technology will be involved to help secure these data in a password protected system. Sharing or reuse of data will not be performed. Records will be stored in a locked filing cabinet in a secured office in Neonates at Perth Children's Hospital. The study data will be retained per the Western Australia health guidelines. Data collected will be accessed only by the authorized members of the study team named on the HREC application for the study.

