### Statistical methods

Table 3 gives a description of the timing and method of assessment of the efficacy and safety parameters. The ultrasound operator and examiner will be blinded to the study.

**Table 3 t3:** Timing and method of assessment of the efficacy and safety parameters

		Measured by	Analysis
Primary efficacy outcome			
	Change in postintervention ipsilateral radial arterial diameter from baseline	Ultrasound at the site of cannulation measured at time of randomization of glyceryl trinitrate/placebo patch and 30, 45 or 60 minutes postintervention	ANCOVA
Secondary outcomes			
	Cross-sectional radial artery diameter in the ipsilateral limb	Measured postintervention by ultrasound	Linear regression
	Percentage change from baseline in radial arterial diameter in ipsilateral limb	Ratio of the postintervention to baseline radial arterial diameters as measured by ultrasound	Linear regression
	Change in the radial artery diameter in the contralateral (no intervention) limb from baseline	Difference and ratio of the radial artery diameter measured at baseline and postintervention	Mixed effects regression modeling of radial artery diameters in both limbs.
Safety outcomes			
	Blood pressure	Systolic blood pressure monitored every 15 minutes	Mixed effects regression modeling of patient trajectories
	Methemoglobinemia	Monitoring of the oxygen requirement and a blood gas analysis if the oxygen requirement increases	Mixed effects regression modeling of patient trajectories

ANCOVA - Analysis of covariance.

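### Blinding of the ultrasound operator to study group is not secured for the 30, 45 and 60 minute comparison, because the scan time is the group; GTN versus control stays masked

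*Protocol article*

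**What the plan says.** The Study endpoint section states: "The operator will be an experienced neonatologist blinded to the study group". Data collection methods repeats the claim in nearly the same words. Two other sections word it differently. Under Blinded staff, the measurements are "performed by an operator who will be blinded to the intervention". Statistical methods adds a second role without describing it: "The ultrasound operator and examiner will be blinded to the study".

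The Interventions section defines the active groups by duration alone, with the patch applied "for 30 minutes (Group A, n = 15), 45 minutes (Group B, n = 15) or 60 minutes (Group C, n = 15". The control group wears a bandage without a patch "for 30 minutes (n = 5), 45 minutes (n = 5) or 60 minutes (n = 5) to ensure blinding". Diameters are measured "at baseline before application of the GTN patch/bandage with no patch and at 30 minutes, 45 minutes or 60 minutes after application", so each infant's follow-up scan falls at the allocated duration.

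The third objective uses the mean within-patient changes "to inform the choice of the optimal duration of GTN patch application in the context of cannulation in neonates". Data management confirms that images are kept: "The trial involves the collection of clinical data and radial artery images by ultrasound measurement".

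**The concern.** If groups A, B and C differ only in duration, and the follow-up scan happens when that duration ends, anyone who knows the time since application knows which of the three an infant would be in if it received GTN. Blinding to study group then cannot hold for the comparison among A, B and C unless elapsed time is hidden, and no such step is described.

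The endpoint is a sub-millimetre ultrasound reading; the assumed untreated mean is 0.76 mm. The Sample size section cites a study in children aged 2 to 8 years in which the radial artery widened by 40% at 30 minutes and 70% at one hour, so a reader may expect more dilation at longer durations. If readings lean that way, some of any apparent gain with duration would be artefact. Likewise, a reader who knows which image is baseline and which is follow-up could lean towards a larger change. What is at stake is the patch time carried into the next trial and the estimate of absolute dilation set against the 25% hypothesis.

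**Working it through.** **1. The plan's own figure.** The Sample size section gives 15 per group, SD 0.18 mm, a difference of 0.19 mm, alpha 0.05 and power above 80% for a four-group ANOVA. With all three GTN means 0.19 mm above control, the noncentrality is 15 × 0.75 × 0.19² / 0.18² = 12.5 on 3 and 56 degrees of freedom, and the power is 83.0%. The figure reproduces, and nothing here changes it. The same SD and group size are used below.

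**2. What scan time reveals.** Inputs are the planned counts from Interventions: 15 GTN infants and 5 controls at each duration.

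| | Scan time unknown | Scan time known |
|---|---|---|
| Chance of GTN | 45/60 = 75% | 15/(15+5) = 75% |
| Best guess of exact group | 15/60 = 25% | 15/20 = 75% |
| Groups still possible | A, B, C, D | two: A or D, B or D, C or D |

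Time gives nothing away about GTN versus control. It fully separates A from B from C.

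**3. Scale of the duration signal.** If the cited 40% and 70% applied to a 0.76 mm artery, the gain from 30 to 60 minutes would be 0.76 × (0.70 − 0.40) = 0.228 mm, or 0.114 mm per 15-minute step. These percentages come from older children, so this gives scale only and is not a prediction for neonates.

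**4. Illustration under an assumed drift.** The documents give no reading bias. Suppose the three GTN durations are truly equal and readings rise by b per 15-minute step. The shift must grow with duration to matter here, since a constant shift creates no trend. For a three-group F test with 15 per group and SD 0.18 mm, the noncentrality is 15 × 2b² / 0.18².

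| Assumed b (mm per step) | Chance of rejecting at nominal 5% |
|---|---|
| 0.01 | 5.7% |
| 0.02 | 7.7% |
| 0.05 | 24.0% |

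**5. Can the controls correct a drift?** A reader who cannot tell GTN from control should shift both alike at a given time, so subtracting the controls within each duration removes the shift on average. The standard error of a difference between two control durations is 0.18 × √(2/5) = 0.114 mm, as large as the whole step in item 3. If baseline and follow-up correlate at 0.8 (assumed), the SD of change is 0.18 × √(2 × 0.2) = 0.114 mm and that standard error is 0.114 × √(2/5) = 0.072 mm, still above a 0.05 mm drift.

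**6. Change from baseline.** The 25% target is 0.25 × 0.76 = 0.19 mm. A follow-up reading shift of 0.03 to 0.05 mm (assumed) would be 16% to 26% of it (0.03/0.19 and 0.05/0.19). A shift common to all arms cancels in GTN minus control, but not in the within-group mean change.

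**The case against.** The best defence is that study group may simply mean GTN or control. Interventions and Allocation concealment both speak of two groups, the patient characteristics table has two columns, and the primary outcome compares GTN with placebo. On that reading the blinding claim is true, and the control durations were evidently split to make it so. This stands for the primary comparison. It does not settle the wording, because Interventions also labels four groups A to D, and the third objective depends on the contrast among three of them.

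A reader might infer that one person performs both scans and measures the diameter live with the duration in view. The documents do not say so. The assessment table names a blinded operator separately for each scan, images are stored, and the blinded examiner may be a separate reader. How images are read is also a detail that an article may leave to the full protocol. What stands against the article is narrower: it asserts blinding to study group where its own schedule would reveal duration to anyone who knows the elapsed time.

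A reader might also infer that a spurious duration trend could never be told from a real one. That is too strong, since the duration-matched controls should carry the same shift. The correction is possible in principle but imprecise with five controls per time, and the third objective is framed as within-patient means, not control-adjusted ones.

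Finally, the 40% and 70% figures are cited to show that a 25% increase is a modest target. The article does not itself predict a gradient with duration in neonates.

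**Conclusion.** The point holds in limited form. The claim of blinding to study group is not secured for the comparison of 30, 45 and 60 minutes, or for knowledge of which scan is baseline. It is secured for GTN versus control by the 5/5/5 control split, provided the planned counts are kept, so the documents do not support reading this as a threat to the primary comparison. No power or sample-size figure changes.

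The size of any bias is unknown. The rejection rates above rest on an assumed drift and on the cross-sectional SD of 0.18 mm; they show what a small differential shift could do, not what will happen. The change is still worth making: informing patch duration is a stated objective, three of the four arms differ only in duration, and masked reading can use material the trial already keeps.

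**What to change.** Take the diameters used for analysis from the stored images. Before reading, remove infant identity, clock time, duration and baseline/follow-up labels, and put the images in random order. The existing blinded operator can do this after a delay, or the examiner named in Statistical methods can, with that role described. Limit the blinding statement for live scanning to GTN versus control. If the full protocol already provides for masked reading, one sentence in the article saying so is enough.

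The cost is some relabelling, reading time and a delay before diameters are available. No extra infants, scans or staff are needed, and the patch schedule is untouched. One limit remains: masked reading protects the measurement, but probe placement and choice of image are still made by an operator who may know the elapsed time.
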